### Intervention

HTH intervention protocols specifically focused on CHD risk reduction. Non-CHD-related conditions remained the responsibility of the patient's PCP, although we often facilitated having the primary care provider address specific patient needs.

#### Immediate intervention

HTH case-management intervention was based on the latest guidelines for the management of CHD risk factors, particularly those reflecting cholesterol management [22,23], hypertension [24], physical activity [25], diabetes [26], aspirin therapy [27,28], smoking [29], obesity management [30], and primary and secondary CHD prevention [31,32]. Specific lifestyle and medical protocols for case managers were developed from these guidelines and continue to be updated based on new evidence. Each patient was managed by a nurse practitioner/registered nurse and a dietitian. Guided by the intervention protocols, the intensity of case management was individualized based on patient risk profile, patient preferences, and available resources within the community. The aim for each patient was to improve individual risk factors and reach recommended goals. Supervised by two physicians and a senior nurse practitioner, the case managers reviewed, adjusted as necessary, and monitored medical therapies in accordance to guidelines and the SMMC formulary. Lifestyle modification was strongly emphasized as a critical component of achieving CHD prevention goals. In particular, dietary management was emphasized, including recommendation of a low saturated fat (less than 7% of caloric intake), low cholesterol (< 150 mg/day), mainly plant-based diet with calorie restrictions for overweight/obese persons. Stress management and coping skills along with physical activity also was emphasized, including recommendations of a regular exercise regimen (≥ 30 minutes of moderate intensity on most days). Cigarette smokers were encouraged to join a stop smoking program that may include use of the nicotine patch or other medications. Additionally, nicotine replacement pharmacotherapies were prescribed, when appropriate, to current smokers. Long-term adherence to these strategies and to medication therapies was stressed and evaluated at each appointment.

#### Delayed intervention

For the first 15 months following randomization, Delayed Intervention patients were expected to continue receiving on-going care from their PCPs. They received a folder at the conclusion of the baseline visit including handouts from the American Heart Association containing basic information about cardiovascular disease and a risk factor description sheet listing their biophysical measurements recorded at the baseline appointment as well as the ideal values for each measurement. They were told that they would be contacted by phone at 7 months and would begin case management intervention at 15 months. In addition, all PCPs received a letter outlining the CHD risk reduction goals recommended in the latest national guidelines.

### Statistical analysis and hypothesis testing

The primary hypothesis of the trial is that Immediate Intervention participants will experience greater reductions in 10-year CHD risk based on Framingham risk probability (primary outcome) than will Delayed Intervention participants. To test the primary hypothesis, we will compare Immediate Intervention participants relative to Delayed Intervention participants in a random-effects regression using SAS PROC GLIMMIX. The dependent variable will be the standardized Framingham risk score at 15-month follow-up. Initially, covariates will be limited to the baseline risk score and intervention status. So we will model participant i (i = 1, 2,..., n_jk_) under the care of physician j within clinic k as:

(1)     Risk_1ijk _= b_0 _+ b_1_Risk_0ijk _+ b_2_Int_ijk _+ α_j _+β_k _+ e_ijk_

where **Risk_1ijk _**is the standardized risk score for the i-th participant at 15 months (time 1) cared for by physician j in clinic k, **Risk_0ijk _**is the risk score at baseline (time 0), **Int_ijk _**is the intervention vs. control status of the i-th participant in the same clinic and under the same physician, **b_0 _**is a constant term, **b_1 _**is the coefficient associated with impact of baseline risk, and **b_2 _**is the coefficient associated with the impact of the intervention. **α_j _**represents the random effect caused by physician j and **β_k _**is the random clinic effect. The error term **e_ijk _**follows normal distribution, N(0, σ^2^). The analysis will be conducted on an intention-to-treat basis. The risk scores of participants lost to follow-up will be set to the baseline or interim values. Alternative methods for handling missing data, such as multiple imputation, may be used if appropriate. Our primary hypothesis will be confirmed if the coefficient associated with the intervention (**b_2_**) is significantly less than 0, implying that the intervention decreased CHD risk scores independent of the baseline level.

In addition, we will evaluate a number of secondary topics including: a) baseline differences in CHD prevention practices, b) moderators and mediators of the intervention effect, c) durability of the intervention effect, and d) cost effectiveness of the intervention. For example, some of the secondary hypotheses we will be testing include a) at baseline, CHD prevention practices within the SMMC fell significantly short of attaining guideline-based goals for a range of risk factors; b) at baseline, adherence to prevention guidelines varied directly by SES with adherence being least likely among participants of the lowest SES; c) implementation of the intervention had a greater impact on participants of lower SES thus resulting in a reduction on the magnitude of socioeconomic disparities in CHD prevention; d) changes in patient dietary and exercise habits were the largest mediators of the impact of the intervention; and e) the change in risk factors attributable to intervention was sufficient to achieve reasonable cost-effectiveness relative to other medical therapies.

In the current manuscript, we presented comparisons of baseline characteristics between the two study arms. All statistical analyses were performed in SAS for Windows (SAS Institute, Cary, NC). Frequency distributions, percentages in each group of categorical variables, and means and quartiles for continuous variables were generated for both intervention groups. Student's *t *tests were performed on continuous variables and χ^2 ^tests on categorical variables to assess comparability between the intervention groups at baseline. Statistical significance was set at *p *< 0.05 (two-tailed).

We will add appropriate covariates into equation (1) to perform the testing of the secondary hypotheses related to moderators and mediators of the intervention effect. For example, these covariates may include SES, change in caloric intake, and change in physical activity. The cost-effectiveness analysis will include: measurement of costs, measurement of changes in quality-adjusted life years (QALYs), and calculation of a cost-effectiveness ratio with an appropriate confidence region. The cost of implementing HTH will be estimated based on the cost of HTH staff time whereas the cost of implementing usual care will be derived from SMMC administrative records. We will estimate a statistical model of QALY changes based on the change in risk of death and, among survivors, the reduction in quality of life due to non-fatal events, which will be approximated using the collected health care utilization data. Using the cost and QALY figures we will estimate an incremental cost-effectiveness ratio, representing the cost per QALY due to the intervention, and a 95% confidence region surrounding the cost-effectiveness ratio using a bootstrapping method. Sensitivity analyses will be performed by varying the underlying model assumptions.

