### Study design

HTH is a 5-year project that consists of a randomized controlled clinical trial in the first 4 years and a transition phase in the last year. The 2-armed clinical trial (Immediate vs. Delayed Intervention) was designed to enroll 400 patients. In an intention-to-treat analysis, this sample size yields 87% power to detect a mean change of 5 points in the Framingham risk score, with an SD of 10, at an α level of 0.01 after accounting for a 25% loss to follow-up.

Participants in both intervention groups continue to receive usual medical care throughout the study period. In addition, participants randomized to Immediate Intervention receive intensive case management for CHD risk reduction for 15 months and then a maintenance program for a minimum of 12 months to assess the durability of initial intervention changes. Participants randomized to Delayed Intervention serve as control for Immediate Intervention patients for the first 15 months and then receive intensive case management for 15 months. The switching-over design not only addresses ethical concerns about withholding treatment from half the study sample, but will also enable us to assess whether the intervention had equal impact whether provided to a naïve population or to a group followed in usual care for 15 months. We will compare change in CHD risk from baseline to 15 months for Immediate Intervention with that from 15 months to 30 months for Delayed Intervention. Similar magnitudes of change in CHD risk between the two study arms would imply that the Delayed Intervention arm was not notably contaminated by the intervention and measurement process and that no noteworthy differences were caused by the 15-month difference in time *per se*.

Immediate Intervention patients who complete their 12-month maintenance period and Delayed Intervention patients who complete their 15-month case management period remain under maintenance case management until they are fully transitioned back to the care of the SMMC in the last year of the project. In addition to patient transition, we will also transition the HTH case management model, as guided by outcomes data from the clinical trial, into an ongoing disease management program operated by SMMC. By including this transition phase, we will be able to assure continuity in patient care and also test the feasibility and effectiveness of implementing our intervention in a community practice setting.

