### Study measurements

The primary outcome measure is the absolute CHD risk over 10 years. For participants without known CHD, the Framingham risk assessment algorithms published by Wilson et al. [33] will be used to estimate the 10-year risk probability of CHD on the basis of sex, age, systolic blood pressure, total cholesterol (TC), cigarette smoking status, and diabetes status. For participants with existing CHD, their 10-year CHD risk will be extrapolated from 2-year probability estimates [34] after accounting for aging effect and censoring individuals with new-onset CHD as time elapses. Secondary guideline-based outcome measures include low-density lipoprotein cholesterol (LDL-C), high-density lipoprotein cholesterol (HDL-C), systolic and diastolic blood pressure, hemoglobin A1c (HbA1c), physical activity, smoking status, body mass index (BMI), dietary intake of total and saturated fat and fruits and vegetables, use of recommended medications (*e.g.*, aspirin, statins, thiazide diuretics, beta-blockers, and angiotensin-converting enzyme inhibitors [ACEIs]/angiotensin receptor blockers [ARBs]).

Outcome measurements are designed to occur at baseline and 15 months for all patients, at 27 months for Immediate Intervention, and at 30 months for Delayed Intervention patients. HTH case managers, including one nurse practitioner, two registered nurses, and two registered dietitians, completed all baseline measurements, which consisted of biophysical measurements, and lifestyle, social, and demographic questionnaires. Baseline visits were conducted in one or two clinic visits, depending upon patient and case manager schedules.

Height was measured by a wall stadiometer and weight by a digital balance scale. Both of these measures were taken without shoes and while wearing light clothing. BMI was then calculated (in kg/m^2^). Waist circumference (in cm) was measured in standing position using a cloth tape measure placed at the level of the iliac crest. Blood pressure was measured in both arms, using the brachial artery, after 10 minutes of sitting in a relaxed position, and the average of two readings was used. After ascertaining that the patient had fasted for ≥ 12 hours, a finger stick blood sample was obtained for measurement of plasma TC, HDL-C, LDL-C, triglyceride (TG), and glucose levels using the Cholestech LDX point of service testing system (Cholestech Corporation, Hayward, CA). Plasma HbA1c was obtained utilizing the Cholestech GDX.

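### The primary missing-data rule lets lost participants take a baseline or an interim score without saying which; interim readings would in practice come from the Immediate arm only, so the rule can bias the main contrast

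*Protocol article*

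**What the plan says.** All references are to the Protocol article.

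- *Statistical analysis and hypothesis testing*: the 15-month risk score is regressed on baseline score and intervention status, with random physician and clinic effects, by intention to treat. For missing outcomes, "The risk scores of participants lost to follow-up will be set to the baseline or interim values". The next sentence adds: "Alternative methods for handling missing data, such as multiple imputation, may be used if appropriate".
- *Study measurements*: "Outcome measurements are designed to occur at baseline and 15 months for all patients". The later measurements, at 27 or 30 months, fall after the primary time point. The same section describes calls at 7 and 22 months about health care use, the only data it describes as interim.
- *Delayed intervention*: these patients stay with their usual physicians for 15 months. "They were told that they would be contacted by phone at 7 months and would begin case management intervention at 15 months".
- *Immediate intervention*: case managers monitor and adjust therapy and assess adherence at each appointment. The exclusion criteria in Table 1 imply appointments roughly every one to two months.
- *Study design*: 400 patients are planned in two arms. The power is given as 87% for a difference of 5 points on the risk score; the remaining assumptions read: "with an SD of 10, at an α level of 0.01 after accounting for a 25% loss to follow-up".

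**The concern.** The rule names two different values and gives no criterion for choosing between them. A call about health care use cannot yield a Framingham score, so a score dated between baseline and 15 months needs a clinical reading. The only study contacts described that could produce one are the case-management visits. If those readings are used, a lost Immediate patient can contribute a value taken during the intervention while a lost Delayed patient contributes the baseline value. Any fall in risk shared by both arms, such as regression to the mean, would then be credited to one arm only.

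The plan allows for a quarter of participants being lost, so this sentence fixes the primary outcome of up to one patient in four. Multiple imputation is optional, so the method could be chosen after the data are seen.

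**Working it through.** **Inputs.** From the article: 400 planned, 419 randomized (212 and 207), effect 5 points, SD 10, alpha 0.01, 25% loss. Assumed: 1:1 planned allocation, two-sided test, correlation 0.7 between baseline and 15-month score, the size of any common trend, loss by arm where unequal, and the share of lost Immediate patients with an interim reading. Physician and clinic effects are ignored.

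**1. The stated power.**
- Completers only, 150 per arm: SE = 10 × √(2/150) = 1.155; 5/1.155 = 4.330; 4.330 − 2.576 = 1.754, giving 96.0% (95.8% with the t distribution).
- All 400 analysed, with the lost quarter contributing no change: effect = 0.75 × 5 = 3.75; SE = 10 × √(2/200) = 1.0; 3.75 − 2.576 = 1.174, giving 88.0% (t: 87.7%).

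The second is close to the stated 87%; the first is not. The design therefore appears to assume baseline values for every lost patient. This is not proof: 87% needs about 109.7 per arm at 5 points, so 150 per arm with a design effect of 150/109.7 = 1.37 would also give it. The article mentions no design effect in its power statement.

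**2. True effect of -5 points, 25% loss in each arm.** Let q be the share of lost Immediate patients given an interim value and f the interim effect as a fraction of 5.

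Estimate = −(0.75 × 5 + 0.25 × q × f × 5) = −(3.75 + 1.25qf)

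- Baseline only (q = 0): -3.75.
- q = 1, f = 0.5: -4.375.
- q = 1, f = 1: -5.0.

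The choice of value moves the estimate by up to 1.25 points, a quarter of the design effect. If lost patients would have kept the full benefit (truth -5), interim values reduce the error. If they lost it by 15 months (truth -3.75), interim values overstate the effect by up to 1.25.

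**3. No true effect, common 2-point fall, interim values in the Immediate arm only.** Bias = 0.25 × (−2) = -0.5 points.

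For the standard error with a quarter of outcomes equal to baseline, the slope on baseline is 0.25 + 0.75 × 0.7 = 0.775. Residual variance is 100 × (1 − 0.775²) = 39.9, so the residual SD is 6.32. SE = 6.32 × √(1/212 + 1/207) = 0.62. Taking the same SE here, 0.5/0.62 = 0.81, and the two-sided rejection rate at nominal 1% is Φ(−2.576 + 0.81) + Φ(−2.576 − 0.81), about 3.9%. Simulations of this setting gave 3.3% to 4.4%.

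**4. Baseline values in both arms, no true effect, common trend t.** Bias = (loss in Delayed − loss in Immediate) × t.
- Equal loss: 0. Simulated false positives were 1.1% at nominal 1%, with model and empirical standard errors both 0.62.
- Immediate 20%, Delayed 30%, t = −2: 0.10 × (−2) = -0.2.
- Immediate 15%, Delayed 35%, t = −2: 0.20 × (−2) = -0.4; simulated false positives about 3% at nominal 1%.
- The same rates reversed: +0.4, against the intervention.

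**The case against.** The strongest reply has three parts, and much of it stands.

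- **Baseline carry-forward is conservative and seems planned.** With equal loss and no effect it keeps the nominal error rate; with a true effect it attenuates. The power calculation appears to include that attenuation. This stands, so the difficulty lies in the interim option and in unequal loss.
- **One-arm availability is an inference.** No sentence says that case-management readings are stored as study data, and the full protocol may define the source of interim values. This also stands. But the article schedules no counterpart for the Delayed arm, and it states the rule for the primary outcome rather than leaving it to another document.
- **The harmful scenarios use assumed inputs.** The common fall, loss by arm and availability of interim values are not in the article. The sizes are therefore conditional.

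A reader might also infer more than the article supports:

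- *That the interval is too narrow because imputed values count as observed.* Under baseline carry-forward with equal loss and no effect, model and empirical standard errors agree at 0.62. A smaller standard error than the one from completers is not by itself an understated one.
- *That freezing age at baseline distorts the result.* Ageing is common to both arms and cancels at equal loss.
- *That deaths are scored as no change.* The sentence concerns loss to follow-up and does not mention deaths.
- *That the rule must favour the intervention.* Steps 2 and 4 show that it can go either way.

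**Conclusion.** The point holds as a risk of bias, not as a demonstrated bias of known sign. The primary rule leaves the choice of value and the source of interim values undefined, and the described schedule makes it likely that only one arm could supply an interim reading. Discretionary multiple imputation does not cure this, because it neither replaces the rule nor fixes when it would be used.

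At 25% loss, the choice between the two values can move the estimate by up to about 1.25 of the 5 design points. With no effect, an assumed common fall of 2 points and interim values for every lost Immediate patient, the bias is about -0.5 and the false-positive rate three to four times the nominal 1%. Under baseline values alone, an assumed 15% versus 35% loss with the same fall gives about 0.4 points, with the sign set by which arm loses more. Fewer interim readings, a smaller trend or more equal loss shrink these figures.

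**What to change.** Replace the carry-forward sentence with one prespecified primary method:

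- Multiple imputation under missing at random, done by arm from the baseline risk components and the randomization factors (gender, ethnicity, clinic), or a likelihood-based model.
- State that case-management-visit readings are not used for the primary outcome, because the Delayed arm has no counterpart.
- Keep baseline carry-forward, applied identically in both arms, as a sensitivity analysis.
- Restate the power for the new analysis: about 96% with 150 evaluable per arm, 5 points, SD 10, two-sided 0.01, before any allowance for clustering.

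The cost is some wording, a little programming and a somewhat wider confidence interval. Under the assumptions above, the standard error on observed data alone is √51 × √(1/159 + 1/155) = 0.81, against 0.62 with carry-forward (51 = 100 × (1 − 0.7²); 159 and 155 are 75% of 212 and 207). The estimate is then no longer shrunk toward -3.75 if the missing-at-random assumption is reasonable. No data collection changes.

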### Recruitment

Between October 2003 and April 2005, 1005 patients were referred by physicians at four SMMC outpatient clinics located in Menlo Park, Redwood City, South San Francisco, and Daly City. These four clinics were chosen for geographic proximity, accommodating clinic environment, sufficient patient volume, diverse patient demographics, and established adult primary care services. All data acquisition and case management visits took place at the clinic where the patient usually receives his/her primary care.

Physicians at the study clinics were instructed to refer male and female patients between the ages of 35 and 85 who had CHD, CHD risk equivalents (*i.e.*, abdominal aortic aneurysm, peripheral vascular disease, carotid artery disease, or diabetes mellitus), or moderately to severely elevated levels of major CHD risk factors. We were unable to contact 257 of the 1005 referred patients and an additional 142 declined participation (Figure 1). We screened the remaining 596 patients by phone or at the baseline visit and excluded 143 patients for failing to meet the exclusion criteria. These criteria identify patients with circumstances that may severely limit their ability complete the study protocol or that may confound results of the study. The footnotes in table 1 list percentages by exclusion criteria. During the same phone call, those not excluded were scheduled for a baseline visit. Table 1 enumerates study inclusion and exclusion criteria. Consent forms were available in English and Spanish and the patient's informed consent was obtained before the start of the baseline visit. For patients who spoke a language other than English or Spanish, a family member over the age of 18 or a SMMC staff member served as interpreter. As part of the baseline evaluation, biophysical measures were obtained that further excluded 44 patients not meeting inclusion criteria.

**Table 1 T1:** Inclusion and exclusion criteria.

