**Inclusion criteria**
The patient has CAD or CAD risk equivalent (abdominal aortic aneurysm, peripheral vascular disease, transient ischemic attack, stroke, diabetes, or FBS ≥ 126 mg/dL × 2) and has at least one of following: SBP ≥ 130 mmHg, DBP ≥ 80 mmHg, LDL ≥ 100 mg/dL, HDL ≤ 40 mg/dL, TG ≥ 150 mg/dL, FBS ≥ 126 mg/dL, BMI ≥ 30, or is a current smoker.
The patient does not have CAD or CAD risk equivalent but has at least one of the following: SBP ≥ 160 mmHg, DBP ≥ 100 mmHg, LDL ≥ 190 mg/dL, TC ≥ 240 mg/dL, TG ≥ 500 mg/dL, HbA1c ≥ 8.0%, BMI ≥ 35, or is a current smoker.
The patient does not have CAD or CAD risk equivalent but has at least two of the following: a) SBP ≥ 140 mmHg or DBP ≤ 90 mmHg, b) HDL ≤ 40 mm/dL or TG ≥ 200 mg/dL, c) LDL ≥ 160 mg/dL or TC ≥ 240 mg/dL, d) FBS ≥ 110 mg/dL × 2, or e) male age ≥ 45 or female age ≥ 55 or with positive family history of CAD.

Abbreviations: FBS = fasting blood sugar, SBP = systolic blood pressure, DBP = diastolic blood pressure, LDL = low-density lipoprotein, HDL = high-density lipoprotein, BMI = body mass index, TC = total cholesterol, TG = triglycerides, HbA1c = hemoglobin A1c.

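### Secondary hypotheses (a) and (b) judge baseline guideline attainment in a sample referred and admitted partly on the same risk factors, so they cannot support a general claim about SMMC practice

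*Protocol article*

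**What the plan says.** All references are to the protocol article.

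- **Hypothesis (a)** (Statistical analysis and hypothesis testing): "at baseline, CHD prevention practices within the SMMC fell significantly short of attaining guideline-based goals for a range of risk factors".
- **Hypothesis (b)** (same section): "at baseline, adherence to prevention guidelines varied directly by SES with adherence being least likely among participants of the lowest SES".
- **Referral** (Recruitment): physicians were asked to refer patients with CHD, with a CHD risk equivalent, or with "moderately to severely elevated levels of major CHD risk factors".
- **Entry** (Table 1): a patient with CAD or a risk equivalent qualifies if he or she "has at least one of following: SBP ≥ 130 mmHg, DBP ≥ 80 mmHg, LDL ≥ 100 mg/dL", or has a low HDL, raised triglycerides or glucose, BMI of 30 or more, or smokes. A patient without CAD needs either one more extreme item or two of five lesser items. One of those five is "male age ≥ 45 or female age ≥ 55 or with positive family history of CAD".
- **Removal** (Recruitment): at the baseline visit "biophysical measures were obtained that further excluded 44 patients not meeting inclusion criteria". Figure 1, footnote 3, splits these into 2 with CAD or a risk equivalent and 42 without.
- **Outcomes** (Study measurements): the guideline-based secondary measures include LDL, HDL, blood pressure, BMI and smoking, which are also entry items. They also include use of recommended medications, diet and physical activity, which are not.

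The Discussion acknowledges that the high prevalence of risk factors follows from the design. Nothing in the article limits (a) or (b) to trial-eligible patients or describes an unselected SMMC sample.

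**The concern.** Hypothesis (a) is worded as a statement about a county health system, but the evidence comes from patients who reached the sample partly because a risk factor was out of range. A significant shortfall would mix the quality of SMMC care with the effect of the referral and entry rules, and the reader could not separate them.

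Hypothesis (b) is already worded about participants, so generalization is the lesser problem there. The difficulty is that risk-factor attainment helps decide who is in the sample, so comparing it across SES groups conditions on part of the outcome. A weak or absent gradient could then be an artefact. Disparity reduction is a stated aim of the project, so these baseline statements are likely to be quoted.

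**Working it through.** **1. Counts.** 2 + 42 = 44, which agrees between Recruitment and Figure 1. 419 randomized + 44 removed = 463, and 44/463 = 9.5%. The preceding flow does not agree with itself: 1005 − 257 − 142 = 606, but the text gives 596. Then 606 − 143 − 44 = 419, whereas 596 − 143 − 44 = 409.

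**2. What entry forces.** The first two routes each need an out-of-range item or smoking. The third needs two of five items. Age or family history together make one item, so at least one blood pressure, lipid or glucose item must also be met. Hence every participant misses at least one entry limit. The exception is the third route's diastolic item, printed with a less-than-or-equal sign. Read literally it would admit patients with low values, and it must be reconciled with the other thresholds in Table 1.

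**3. What entry does not force.** I interpolated linearly between the Table 3 quartiles within each arm and weighted by 212 and 207. For LDL below 100:
- Immediate: 0.25 + 0.25 × (100 − 81)/(102 − 81) = 0.476
- Delayed: 0.25 + 0.25 × (100 − 80)/(103 − 80) = 0.467
- Pooled: about 47%

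In the same way, about 44.5% have SBP below 130 and about 66.5% have HDL above 40. The article reports 16% current smokers, so 84% are not. No single factor's attainment is fixed by entry.

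**4. Where screening bit.** Diabetes, a risk equivalent, was present in 63%: 0.63 × 419 ≈ 264.
- With CAD or a risk equivalent: 2 removed of at least 264 + 2 = 266, so at most about 0.8%.
- Without: 42 removed of at most (419 − 264) + 42 = 197, so at least about 21%.

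**5. Upper limit on the screening effect per factor.** Suppose all 44 were within every limit. The share off limit is then multiplied by 419/463 = 0.905: LDL ≥ 100 from about 53% to 48%, SBP ≥ 130 from about 56% to 50%, TG ≥ 150 from about 64% to 58%, BMI ≥ 30 from about 69% to 63%. These are lowest possible values, because failing entry is not the same as being at goal (see the objection). Selection at referral comes on top and cannot be quantified from the article.

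**6. Attenuation in (b).** Assumptions (mine, not the article's): K independent factors, each off goal with probability q₁ in higher SES and odds twice as high in lower SES, and entry if at least one factor is off goal. Then P(factor off | entered) = q / (1 − (1 − q)^K).

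Example with K = 4, q₁ = 0.10:
- Lower-SES odds = 2 × 0.10/0.90 = 0.222, so q₂ = 0.182.
- Conditional probabilities: 0.10/0.344 = 0.291 and 0.182/0.552 = 0.329.
- Odds ratio after selection = (0.329/0.671)/(0.291/0.709) ≈ 1.20.

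| q₁ | K = 4: OR (higher-SES screened out) | K = 8: OR (higher-SES screened out) |
|---|---|---|
| 0.10 | 1.20 (66%) | 1.38 (43%) |
| 0.20 | 1.39 (41%) | 1.68 (17%) |
| 0.30 | 1.56 (24%) | 1.86 (6%) |
| 0.50 | 1.82 (6%) | 1.99 (0.4%) |

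A true odds ratio of 1.5 becomes 1.10 to 1.49. For a composite of any entry limit missed, no gradient can appear at all, since everyone misses one (subject to the diastolic item in step 2).

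**The case against.** The strongest reply is that the selection is much weaker than it first looks, and most of its parts stand.

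- A reader might infer that patients were admitted only because they missed goals. The article does not support this. Referral of patients with CHD or a risk equivalent carried no condition of poor control, and CAD status, diabetes, age and family history all bear on entry.
- A reader might infer that (a) is true by construction and cannot fail. It concerns a range of risk factors, and step 3 shows that attainment of each is an empirical matter.
- The 44 removed patients cannot be counted as meeting guideline goals. Limits for patients without CAD were much looser (for example SBP ≥ 160 or LDL ≥ 190 as single items), and under the two-item rule a patient with one raised item also fails entry.
- A reader might infer that an SES gradient could be reversed. The model in step 6 shows attenuation only, and the article offers no evidence of reversal.
- Prevention practice and adherence naturally include medication use, which is listed as an outcome, was asked about specifically in patients with CHD or diabetes, and is already reported by indication.
- The hypotheses are offered as examples, and their tests may be detailed in documents not shown.

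The last point does not dispose of the matter. The target of inference in (a) is stated in the article, and a later choice of test cannot make a referred and screened sample represent SMMC practice. Nor does collecting medication data help unless the claim is tied to it.

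**Conclusion.** The concern holds in a limited form. The trial sample cannot support an unqualified significance claim that practice within the SMMC falls short, because referral and entry rested partly on the factors being judged. The share missing at least one entry limit is fixed by design; attainment of each single factor is not.

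For (b), comparing risk-factor attainment by SES partly conditions on the outcome and can attenuate a true gradient. The range of 1.20 to 1.99 for a true odds ratio of 2.0 rests on assumed independence, equal effects and assumed off-goal rates. The documents do not say where in that range, if anywhere, the trial lies. Screening selection is close to negligible among patients with CAD or a risk equivalent (at most about 0.8% removed) and material among the rest (at least about 21%). Referral selection is of unknown size in both. The randomized primary comparison is not touched.

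**What to change.** 1. Restate (a) and (b) as applying to trial-eligible patients, with no inference to SMMC practice generally.
2. Report risk-factor attainment descriptively, factor by factor and separately for patients with and without CAD or a risk equivalent. Do not use a composite of missed limits.
3. Base any formal test on measures not used for entry and already collected: use of aspirin, statin, beta-blocker and ACEI/ARB among patients with the indication. The article already reports one such figure, aspirin use of 64% in CVD or diabetes. Referral still shapes who is in the sample, so these tests too should be stated as concerning trial-eligible patients.
4. Do not try to repair the problem by taking all 463 patients as the denominator. That leaves referral selection in place, SES data for the 44 are not documented, and the screening counts (606 against 596) must be reconciled first.
5. Reconcile the direction of the diastolic item in Table 1 with the other thresholds.

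The cost is rewording and a narrower secondary claim. No new data are needed.
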